##### Older adult participant measures

The primary measure of effectiveness is mental functioning of the older adult participants as measured by the mental component score (MCS) of the Veterans Rand 12-item health survey (VR-12) [55]. Secondary outcome measures include: the physical component score (PCS) of the VR-12 [55] to measure changes in physical functioning; the Centre for Epidemiologic Studies Depression Scale (CESD-10) [56] to determine the presence and severity of depressive symptoms; the Generalized Anxiety Disorder Scale (GAD-7) [57] to determine the presence and severity of anxiety; the Personal Resource Questionnaire (PRQ-2000) Part Two [58] to measure perceived social support; and a subset of questions from the Patient Provider Communication Questionnaire (PPC) [59], the Client Centered Care Questionnaire (CCCQ) [60], the Intermediate Care for Older People Home-Based-Integrated Care Patient-Reported Experience Measures (IC-PREMs) [61], and an Unmet Care Needs questionnaire developed for the purposes of this study to measure patient experience. A complete copy of the questionnaire that includes these measures is provided as supplementary data (see Additional file 1).

##### Caregiver measures

Caregivers of older adult participants will be assessed for caregiver strain using the Modified Caregiver Strain Index (CSI) [62]. Other caregiver outcome measures include: the CESD-10 [56] to measure the presence and severity of depressive symptoms, the GAD-7 [57] to measure the presence and severity of anxiety, the mental and physical component score of the VR-12 [55] to measure health-related quality of life; and a subset of questions from the PPC [59], the CCCQ [60], the IC-PREMs [61], and the Unmet Care Needs questionnaire developed for the purposes of this study to measure caregiver experience. A complete copy of the questionnaire that includes these measures is provided as supplementary data (see Additional file 2).

##### Cost of use of health and social services

The study will link participants to Institute for Clinical Evaluative Sciences (IC/ES) administrative databases to identify the use of emergency room visits, hospital admissions, use of family physicians, physician specialists, and home care services, and transfers to long-term care. In addition, the Health and Social Services Utilization Inventory (HSSUI) [63] will be used to measure the utilization of health and social services as reported by study participants and caregivers over the duration of the study. The HSSUI consists of questions about the respondent’s use of six categories of direct healthcare services: a) primary care; b) emergency department and specialists; c) hospital days; d) seven types of other health and social professionals; e) prescribed medications; and f) lab services. The data from the HSSUI will be used in combination with the IC/ES administrative data as a back-up in case we are unable to obtain IC/ES data at all three timepoints.

The six-month cost data will be derived from the product of “quantity” data reported on the HSSUI and 2015–2016 “price” data obtained by our team for the HSSUI [64]. The costs of use of health and social services will include the costs associated with delivery of the nurse-led intervention. This will form the basis of the cost-analysis, from a societal perspective that will compare changes in the costs of use of health and social services between participants in the intervention and control groups from baseline to 6- months, and from 6-months to 12-months post intervention. A complete copy of the HSSUI questionnaire is included as supplementary data (see Additional files 1 and 2). Table 1 provides an overview of the effectiveness evaluation, including the outcome, measures, group, and tiepoint for data collection.

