The CAST intervention has the potential to inform policy decisions concerning the provision of transitional care for older adults with MCC and depressive symptoms transitioning from hospital to home. Given the rapid increase in the number of older adults living in the community, the challenges of meeting the complex care needs of older adults with MCC and depressive symptoms have the potential to place extensive burdens on a health care system that is already under strain. In Ontario, the jurisdiction where CAST is being evaluated, a recent expert advisory panel on health care reform identified a number of system-level issues the CAST study has the potential to mitigate, including an increase in the number of patients with complex needs, difficulties with system navigation, challenges transitioning between services, and the need for more effective coordination at point of care [83]. Moreover, the level of patient support offered by the CAST intervention has the potential to enable greater independence and aging at home, which is the expressed preference of community-dwelling older adults [3, 84, 85]. This project will have meaningful results for patients as the outcomes will address not only their unmet needs but reflect issues important to them. Further, the study results will support the continued development of our patient- and community-centred research agenda [72, 82]. The use of a pragmatic effectiveness-implementation trial will enhance the relevance of the results for practitioners and policy makers, thereby reducing the research-practice gap and enhance the sustainability and scalability of the intervention.

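### The stated cost rule has no quantity or price for long-term care, although transfers to long-term care are tracked as service use and the cost analysis claims a societal perspective

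*Protocol article*

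**What the plan says.** The section Cost of use of health and social services in the Protocol article makes three statements that bear on this point.

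- **Service use.** Linkage to IC/ES is to identify emergency and hospital use, physician contacts (family physicians and, in the article's words, "physician specialists, and home care services, and transfers to long-term care").
- **Content of the HSSUI.** The inventory asks about "use of six categories of direct healthcare services: a) primary care; b) emergency department and specialists; c) hospital days", followed by "d) seven types of other health and social professionals; e) prescribed medications; and f) lab services".
- **Cost.** The sentence opening "The six-month cost data will be derived from the product of" takes the quantity from the HSSUI. The price is the 2015–2016 "data obtained by our team for the HSSUI". The cost of delivering the nurse-led intervention is added. The result is the basis of a cost analysis described as societal, comparing the arms from baseline (T1) to 6 months (T2) and from 6 to 12 months (T3).

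The same section says that the HSSUI will be combined with the IC/ES data and serve as a back-up if IC/ES data cannot be obtained at every timepoint. Table 1 places utilization and associated costs in one row, names both sources and plans a Mann-Whitney U test. Under Eligibility criteria, patients being discharged to a long-term care home are excluded.

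**The concern.** Use and cost share one row of Table 1, but they do not have the same components. A move to long-term care counts as use, while the cost rule has neither a quantity nor a price for it. If community and hospital contacts fall after the move, that participant can look cheaper than one who stays at home.

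This affects how the result would be read. The Discussion presents the cost analysis as evidence on the economic feasibility of building the intervention into usual care, and says that the support offered "has the potential to enable greater independence and aging at home". If the intervention prevented entries to care, the saving would be missing from the result. If it led to more or earlier entries, the extra cost would be missing. The planned sensitivity analysis for outliers would not reveal either, because it can only examine costs that were entered.

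**Working it through.** **Step 1. Compare the lists.** The HSSUI categories are those quoted above.

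| Component | Identified as use through IC/ES | In the stated cost rule |
|---|---|---|
| Hospital stays | yes | yes (hospital days) |
| Emergency department, specialists | yes | yes |
| Family physician / primary care | yes | yes |
| Transfer to long-term care | yes | no quantity, no price |
| Intervention delivery | not applicable | yes, added separately |

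No HSSUI category is a residential stay, and the named prices are those obtained for the HSSUI. The article gives no rule for turning an IC/ES item into a cost.

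**Step 2. Can entry to care happen during follow-up?** Yes. Discharge to a long-term care home is an exclusion, baseline is assessed after discharge, and randomization follows baseline. Entry is therefore mainly an event after allocation.

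**Step 3. Size of the omission.** The plan states no figure on this point, so there is none to reproduce. With 216 participants allocated 1:1 there are 216 / 2 = 108 per arm. The entry proportion p and the months in care m within a six-month window are assumptions.

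- Entrants per arm = 108 × p. For p = 0.02, 0.05 and 0.10 this is 2.2, 5.4 and 10.8 people.
- Mean cost omitted per participant, in units of one month's long-term care price, = p × m. With m from 1 to 5 it runs from 0.02 × 1 = 0.02 to 0.10 × 5 = 0.50.

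**Step 4. Error in the difference between arms.** This is (p × m in the intervention arm) − (p × m in the control arm).

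- Same entry and same stay: zero. Cost is understated in both arms, but the difference is not biased.
- Entry differing by 2 to 5 points, same stay of 1 to 5 months: from 0.02 × 1 = 0.02 to 0.05 × 5 = 0.25 monthly prices per participant.
- Same entry of 5%, stays of 3 and 1 months: 0.05 × (3 − 1) = 0.10 monthly prices.

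**Step 5. Effect on the planned test.** The Mann-Whitney test uses ranks, so a mean error does not carry over directly. As an extreme case, suppose that costing long-term care moved every entrant, in both arms alike, from the lowest rank to the highest. With entry proportions a and b, the probability that a participant in one arm outranks one in the other would shift by a(1 − b) − b(1 − a) = a − b. A difference of 2 to 5 points gives 0.02 to 0.05. With 108 per arm and complete data, the null standard error of that probability is √(217 / (12 × 108 × 108)) = 0.039. The extreme shift is therefore 0.02 / 0.039 = 0.5 to 0.05 / 0.039 = 1.3 standard errors, and less extreme rank changes would give less.

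**The case against.** The strongest reply is that costing from IC/ES may be intended. The back-up sentence and Table 1 both name IC/ES beside the HSSUI, and the full questionnaire and the price source lie outside the article. This stands as a reason not to claim that the sponsor has ruled out costing long-term care. It does not repair the rule: those places name data sources, while the costing sentence takes its quantities and prices from the HSSUI. Nor is this detail that the article simply leaves elsewhere, because it states the quantity source, the price source and year, the perspective and the one added component.

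Taking quantities from the HSSUI is also defensible, because it keeps total cost independent of a linkage that may be incomplete. That point is accepted and shapes the fix. It is also true that the article speaks of transfers and not of days in care, so time in care would have to be derived.

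A reader might infer three stronger things that the documents do not support:

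- That an entrant carries no institutional cost at all. Hospital days are counted; the gap is long-term care.
- That the comparison of arms is biased in any event. This requires entry or stay to differ by arm, and the documents give no evidence on that.
- That keeping people at home is a formal aim. The Discussion states a potential. The stated purpose concerns the quality and experience of transitions, and the hypothesis gives hospitalization as its example of expensive care.

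**Conclusion.** The point holds for the rule as written. Transfers to long-term care are identified as use, but the stated cost (HSSUI quantity times HSSUI price, plus intervention delivery) contains nothing for them, which does not fit a societal perspective. Cost is understated for any participant who enters care during follow-up. The difference between arms is biased only if entry or length of stay differs between them.

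The size cannot be computed from the documents. The range of 0.02 to 0.50 monthly prices per participant rests on assumed entry of 2% to 10% and stays of 1 to 5 months. The effect on the Mann-Whitney comparison may be modest, since only a few people per arm would change rank. Cost is not the primary outcome, and the primary analysis of mental functioning is unaffected. The matter is still worth settling, because the cost result is meant to inform adoption and the remedy is cheap.

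**What to change.** In the section Cost of use of health and social services, choose one of two courses and say so.

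1. **Cost it.** Add long-term care time, derived from the transfer dates in the IC/ES linkage, multiplied by a stated unit price, for both T1–T2 and T2–T3. Keep the HSSUI-only cost (with intervention delivery) as a sensitivity analysis in case linkage is incomplete.
2. **Leave it out openly.** State that long-term care is not costed, narrow the described perspective accordingly, and report transfers by arm beside the cost result.

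The first course needs one extra unit price and the derivation of time in care from the linked data, and it makes that component depend on the linkage. The second is wording plus one descriptive table row. Neither needs new data from participants, because the transfers are already among the items to be linked.

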### Interventions

#### CAST intervention group

The CAST intervention was designed to complement usual care and consists of usual care plus a tailored patient- and caregiver-centred intervention delivered by a Care Transition Coordinator (CTC) who is a Registered Nurse (RN). The CTC will conduct a minimum of two in-home visits along with a minimum of four telephone calls scheduled to accommodate participant needs and preferences over a six-month period.

Throughout the 6 month duration of the intervention, the CTC will: 1) identify the health care professionals involved in the participant’s circle of care and initiate a plan for regular communication and follow-up with these individuals and organizations; 2) identify and manage the patient’s risk factors for depressive symptoms and other chronic conditions in accordance with evidence-based guidelines [52, 53]; 3) provide system navigation support, coordination, and follow up for participants and caregivers; 4) conduct medication review and management in collaboration with participants, primary care providers and pharmacists using evidence-based best practice guidelines [52, 53]; 5) conduct problem-solving therapy with participants and caregivers using Nezu et al.’s [54] manual; 6) implement social and behavioural activation, which involves assisting and encouraging participants to participate in regular physical activity programs tailored to social and behavioural needs; 7) provide patient and caregiver education; and 8) alert the participant’s primary care provider to the presence of depressive symptoms, dementia, delirium, suicidal ideation, or medication issues. These activities will be completed through direct interactions with participants during home visits and phone calls and indirect activities, (e.g., referring participants to health and social services, communicating with healthcare providers in the participant’s circle of care) completed between scheduled appointments.

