#### Usual care group

Participants allocated to the control group at discharge from hospital to home will receive usual care. Usual care, which varies from site to site, may include recommendations for the patient to see their primary care provider and/or other medical specialists or access home care and/or other health and social services provided in the community after hospital discharge.

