Client-centredness of care	Adapted Client-Centred Care Questionnaire (CCCQ) [60]	PT, CG	T_1_, T_2_, and T_3_	-Descriptive analyses -T1: z test of proportions for group comparison, complete case analysis -T2: z test of proportions for group comparison, complete case analysis
Care experience	Integrated Care Patient-Reported Experience Measures (IC-PREMs) [61]	PT, CG	T_1_, and T_2_	-Descriptive analyses -T1: z test of proportions for group comparison, complete case analysis -T2: z test of proportions for group comparison, complete case analysis
Unmet care needs	Unmet Care Needs questionnaire	PT, CG	T_1_, T_2_, and T_3_	-Descriptive analyses - T1: z test of proportions for group comparison, complete case analysis -T2: z test of proportions for group comparison, complete case analysis
Caregiver strain	Modified Caregiver Strain Index (CSI) [62]	CG	T_1_, T_2_, and T_3_	-Descriptive analyses -T1-T2 (Treatment Effect): ANCOVA, complete case analysis -T2-T3 (Sustainability): ANCOVA, complete case analysis
Utilization of health and social services and associated costs	Institute for Clinical Evaluative Sciences (IC/ES), Health and Social Services Utilization Inventory (HSSUI) [63, 64]	PT, CG	T_1_, T_2_, and T_3_	-Descriptive analyses -T1-T2 (Treatment Effect): Mann-Whitney U test, complete case analysis, Hazard Ratio (95% CI) & Risk Difference (95% CI) for 30, 90 &180-day ED visits and hospital admissions -T2-T3 (Sustainability): Mann-Whitney U test, complete case analysis

*PT = patient; CG = caregiver, *T1 = baseline; T2 = 6-month; T3 = 12 months

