#### Analysis: effectiveness evaluation

Descriptive statistics will be used to summarize outcome values at baseline, 6 months and 12 months. Means and standard deviations will be used for continuous outcomes, and frequency and percentages will be used for categorical outcomes. Intention-to-treat analyses using analysis of covariance (ANCOVA) will be used to assess group differences in continuous outcomes from baseline to T2 in order to determine if the intervention was effective over the intervention period. The outcomes include: PRQ-2000, CESD-10, GAD-7, VR-12 PCS, VR-12 MCS, the PPC, CCCQ, and the IC-PREMs. The ANCOVA model will use the 6-month outcome value as the dependent variable, the group indicator as the independent variable and the baseline outcome value as the covariate. Model results will be expressed as mean group differences with accompanying 95% confidence limits. Quantile regression will also be used to examine the treatment effect over a broader range of values (beyond the mean) for the outcome variables. Assessment of group differences in continuous outcomes from T_2_ to T_3_ will be assessed using ANCOVA and will be aimed at assessing the sustainability of the intervention effects (see Table 1).

Z tests of proportions and McNemar tests will be used to assess changes within each group in the number of participants with acute care episodes and the number of acute care episodes from baseline to T_2_, and from T_2_ to T_3_ Acute care episodes include emergency department visits and hospital admissions. Risk difference (intervention risk – control risk) and accompanying 95% confidence limits will be calculated for 6 months for emergency department visits and hospital readmissions for 6 months. As was noted earlier, acute care episodes will be identified using administrative data from IC/ES, and self-reported data from the HSSUI. Due to the highly skewed nature of cost data, a non-parametric test will be used to compare the change in health and social service use and costs from baseline to T_2_ and from T_2_ to T_3_ for the two groups. Outliers are particularly common for certain healthcare costs such as hospital admissions, thus we will conduct a sensitivity analysis to assess the impact of outliers on the cost comparison.

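### The T2-to-T3 change in cost absorbs the end of CAST's own delivery cost, so it cannot by itself show whether any saving is sustained

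*Protocol article*

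**What the plan says.** All of this is in the protocol article.

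- **What the cost variable contains** (Cost of use of health and social services): "The costs of use of health and social services will include the costs associated with delivery of the nurse-led intervention". Costs are built in six-month blocks: "The six-month cost data will be derived from the product of “quantity” data reported on the HSSUI", multiplied by prices.
- **When delivery cost arises** (CAST intervention group): "Throughout the 6 month duration of the intervention, the CTC will" carry out the listed activities, and "The CTC will conduct a minimum of two in-home visits along with a minimum of four telephone calls" over that period. The usual care section says: "Participants allocated to the control group at discharge from hospital to home will receive usual care".
- **What is compared**: the cost section compares arms on changes in cost "from baseline to 6- months, and from 6-months to 12-months post intervention". The section Analysis: effectiveness evaluation repeats this: "a non-parametric test will be used to compare the change in health and social service use and costs" over the same two intervals.
- **How the second interval is read** (Table 1, row on utilization and costs): "T2-T3 (Sustainability): Mann-Whitney U test, complete case analysis".

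The only sensitivity analysis named for cost concerns outliers. The article does not remove delivery cost from the T2-T3 contrast, does not test months 6-12 cost as a level, and does not test total cost over 0-12 months.

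**The concern.** Counting delivery cost is right when asking what the programme costs. The difficulty comes from taking a change score across the point at which the programme ends. The CAST arm's T2 cost contains delivery cost and its T3 cost does not; the control arm has it in neither. The CAST arm's T2-T3 change is therefore lowered by its own delivery cost whatever happens to service use.

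The contrast carries the label of sustainability, and the Discussion offers the cost analysis to policy makers as evidence on economic feasibility. A relative fall after month 6 could be read as a lasting saving when part or all of it is the programme stopping. The problem lies in the quantity being compared, so it would arise with any test applied to the T2-T3 change, not only a rank test.

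**Working it through.** **The plan's own figures.** The article gives no unit cost, delivery cost or power for cost, so there is no cost figure to reproduce. The sample size supplies only the number per arm. For a difference of 6.5, SD 15.0, two-sided alpha 0.05 (sidedness assumed) and 80% power, the normal formula gives 84 per arm, or 168 in total; 168 / 0.8 = 210, within 3% of the stated 216. After 20% attrition, 216 x 0.8 / 2 = 86.4, so 86 per arm is used below.

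**Expected value of the contrast.** Let C2 and C3 be the mean cost of services other than CAST under usual care in months 0-6 and 6-12. Let c be the mean delivery cost per CAST participant, and s2 and s3 the savings CAST produces in the two periods.

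- CAST change, T2 to T3: (C3 - s3) - (C2 - s2 + c)
- Control change, T2 to T3: C3 - C2
- Difference: D = -c + s2 - s3

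Cases:

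- No effect (s2 = s3 = 0): D = -c
- Fully sustained saving (s2 = s3): D = -c
- Temporary saving only (s3 = 0): D = s2 - c, negative if s2 < c and positive if s2 > c

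The first two cases are the ones a sustainability analysis must tell apart, and they give the same value.

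**Size under no effect.** All cost inputs are assumptions: log-normal six-month costs, 86 per arm, 2,000 simulated trials per setting, two-sided Mann-Whitney test on the T2-T3 change. Setting A uses a coefficient of variation (CV) of 1.5-2.0, between-period correlation 0.3-0.5 and a constant c. Setting B uses mean cost 8,000, CV 1.0-2.0, correlation 0.4 on the log scale, and c varying between participants with an SD of 30%.

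| c as share of mean six-month cost | Rejection, A | Rejection, B |
|---|---|---|
| 0 | 4-5% | 5.0-5.7% |
| 5% (B: 400 / 8,000) | 6.0-7.9% | 6.9-8.0% |
| 10% (B: 800 / 8,000) | 13.2-17.5% | 15.5-16.1% |
| about 20% (B: 1,500 / 8,000 = 18.75%) | 35.8-51.3% | 36.3-38.5% |

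The last row is illustrative only; nothing in the documents supports a share that high. At 10%, almost all rejections favour CAST (15.3% of trials at CV 1.5, against a nominal 2.5% in that direction).

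**Other cases, setting B at CV 1.5** (mean difference in change; significant in CAST's favour):

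- Lasting 10% saving, c = 800: -765; 14%. No effect, c = 800: -882; 15%. Both have expectation -800 and differ only by simulation error.
- Temporary 10% saving (800), c = 1,500: expectation 800 - 1,500 = -700, simulated -762; 22%.
- Temporary 10% saving, c = 800: expectation 0, simulated +46; 6%.
- Temporary 20% saving (1,600), c = 800: expectation +800, simulated +800; 2%.

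**Check of the remedy.** Under no effect, removing c from the change gives rejection of 4.5-5.7% (setting B). Testing months 6-12 cost as a level gives 4-6% (setting A).

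**The case against.** A reader might infer that the 12-month economic result as a whole is biased towards CAST, or that CAST costs will appear to fall whenever its effect does not last. The documents do not support either reading. A lack of lasting effect includes a temporary saving, and if that exceeds c the mean contrast goes against CAST. This case cannot be set aside: the article hypothesises less use of expensive services, and its feasibility study reported fewer hospitalizations, ambulance uses and emergency visits.

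The plan also reports the baseline-to-T2 change, which carries +c against CAST. In expected means that contrast is c - s2, and adding D gives -s3, so someone holding mean changes for both intervals could see the cost enter and leave. Descriptive summaries at each time point and separate analyses of service use and acute-care episodes give further context.

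Finally, the documents fix no delivery cost, participants may decline contacts, and at 5% of mean cost the rejection rate is close to nominal. The article does not say in words to which window delivery cost is booked; months 0-6 follows from the six-month delivery period.

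These points limit the direction, scope and size of the concern. They do not repair the stated test. The two intervals are tested separately on ranks, which do not add up as means do; the acute-care comparison at T2-T3 is described as within group; and no planned test isolates months 6-12 cost. Nor is this detail left to an analysis plan: the article itself states that delivery cost is included, that change is compared, and that the second interval is read as sustainability.

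**Conclusion.** The point holds in a limited form. As written, the T2-T3 cost contrast mixes the end of programme cost with change in service use and cannot by itself show sustainability, because it has the same expectation, -c, under no effect and under a fully sustained saving. It shows a spurious relative fall under no effect or when a temporary saving is smaller than c, and a relative rise in mean cost when a temporary saving exceeds c.

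This conclusion needs only the article's own rules, with delivery cost booked when CAST is delivered. The size is unknown because c is not given. Under no effect and the assumed cost distributions, rejection is about 6-8% if c is 5% of mean six-month cost and 13-18% if it is 10%. One contrast of a secondary outcome is affected; the primary MCS analysis and the baseline-to-T2 cost comparison are not. It should be corrected because the misreading is built into the rule and is cheap to remove.

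**What to change.** In the cost section, in Analysis: effectiveness evaluation, and in the T2-T3 entry of the Table 1 cost row:

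1. For costs, replace the T2-T3 change by a between-arm comparison of the cost incurred in months 6-12 itself.
2. Report the between-arm difference in cumulative cost over months 0-12, including delivery cost. Its expectation is c - s2 - s3, the net cost of the programme over the year.
3. If a T2-T3 change in cost is still shown, compute it without delivery cost and say so.
4. Keep delivery cost in the baseline-to-T2 contrast, and state that it is booked to months 0-6.

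This changes analysis wording only and needs no new data. The drawback is that the 12-month cost result may look less favourable to CAST.
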